### Intervention

2.5

Patients will be submitted to TPNS based on previously described methods.^[28,31]^ A physiotherapist, a member of the research team with experience in this therapy, will supervise all the procedures. Two silicone auto adhesive electrodes (5 × 5 cm) will be applied on each side of the sacrum at the level of S2 to S4 (Fig. 1). The electrodes will be linked to an electrical stimulation device (De Tens/Fes - 2 channels, Neurodyn Portable Ibramed). The maximum level tolerated by the child but without reaching the motor, the point will set the intensity level. A 500-μs, 10-Hz current will be applied 30 minutes daily for 4 or 8 consecutive weeks in the patient's residence.

**Figure 1 F1:**
[figure not shown]
Electrode positioning for transcutaneous parasacral nerve stimulation.

Parents or guardians will be trained to perform TPNS on their children. Training courses and supervised applications will be provided until parents are confident enough to implement TPNS without supervision. From then on, TPNS will be executed daily in the family. During the intervention period, patients will need to attend a supervised session of TPNS every 15 days for a revaluation of the technique and clarification of any doubts.

During the intervention period, patients must maintain all the treatment recommendations (drugs, diets, and behaviors) previously prescribed by the referring physician. Any necessary modifications in treatment during this period will not be avoided or postponed because of the study. Patients must call the research team any changes to the treatment plan during the intervention.

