### Patient selection and recruitment

2.3

The estimated sample size was 28 patients, calculated for a paired *t*-test (before and after intervention), based on an estimated mean increase of 18 defecations per month (according to data from a previous TPNS study 27), an estimated standard deviation of changes = 30, a 2-tailed α = 0.05 and a test power β= 0.85. The sample will include the Pediatric Gastroenterology Outpatient and Pediatric Surgery Outpatient Clinics of the Botucatu Medical School (UNESP). Patients will be invited to participate in an initial consultation to inform them about the research methods and apply eligibility criteria.

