### Eligibility criteria

2.4

The inclusion and exclusion criteria are presented in Table 1.

**Table 1 T1:** Eligibility criteria.

Inclusion criteria	Exclusion criteria
Diagnosis of functional constipation, according to Rome IV criteria (2016) ^[4,5]^	Presence of any organic cause for constipation
Children with age between 7 and 18 yrs old	Children with neurological and/ or cognitive deficits
Patients and/or their guardians who agree to and sign the ICF	Presence of skin lesions in the region of application of the electrodes
Patients aged 11 to 18 who agree and sign the respective SCF	An altered sensation at the electrode application site
Use of cardiac pacemaker	
Children with heart disease or cardiac arrhythmias	
Patients who do not complete the intervention or do not participate in some of the evaluation interviews	

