### Intervention periods and assessment time points

2.7

The intervention period will be 4 consecutive weeks, immediately following the conclusion of the training period. Then, patients and/or their guardians may choose to extend the intervention period for another 4 consecutive weeks until completing 8 weeks of TPNS. The 3 or 4 moments for assessment interviews will be the following: 1 week before the start of the intervention, immediately after the 4 weeks of intervention or immediately after the 4 and 8 weeks of intervention, and 4 weeks after the end of the intervention period, to identify any remaining effects of TPNS.

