### Outcomes

2.9

Data analysis will focus on each assessment moment. The following clinical variables will be used for this analysis: the number of bowel movements per week, the number of fecal incontinence episodes per week, whether diapers or underwear protection is needed, whether defecation medications are needed, special diets, straining and pain while passing stool, presence of fecalomas, presence of abdominal pain, presence of bloody stools, need for enemas, and presence of perianal rashes or dermatitis. We will also analyze the results obtained by all the assessment instruments applied (mBSFS-C, BF-S, FCI questionnaire, AQLCAFI, and PEDsQL 4.0) to evaluate the outcomes of the functional status of bowel habits and the global quality of life.

As a secondary outcome, the applicability of TPNS will also be evaluated through the results of a specific questionnaire^[31]^ (see applicability questionnaire, Supplemental Digital Content 10), taking into account the practical difficulties and possible adverse events involved in using the method. All conditions that may be indirectly involved in the clinical results of TPNS, such as modifications in laxative doses or any clinical or dietary changes, will also be analyzed as secondary endpoints. Figure 2 summarizes the stages of the study and the Supplemental Digital Content 11 (SDC-11) features information about the Standard Protocol Items: Recommendations for Interventionist Tests (SPIRIT).

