## Discussion

3

TPNS can be considered a promising, noninvasive, and safe method to be used as adjunctive therapy for treating constipation.^[18,27–30]^ However, there is a lack of published data that has investigated its use directed to treatment of children with FC.

This study's main objective was to assess the applicability and clinical outcomes of TPNS in children with FC. This study aims to demonstrate the efficacy of this promising method to increase the number of bowel movements and to improve stool consistency, to reduce the number of episodes of retentive fecal incontinence and to improve the overall quality of life indirectly.

Our research group has already developed a similar study to evaluate the applicability and clinical results of posterior tibial nerve stimulation in children with functional constipation.^[31]^ Thus, it will also be possible to compare the results obtained by these 2 minimally invasive neurostimulation methods in this clinical setting.

This study is currently in the planning phase, with the recruitment phase planned to begin in November 2020.

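### Applicability is rated only by families who became confident in home TPNS and completed it, so the result cannot register a family that fails in training

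*Protocol article*

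**What the plan says.** **Training and time zero.** Section 2.5 of the protocol article gives training an end point but no maximum length or number of sessions: "Training courses and supervised applications will be provided until parents are confident enough to implement TPNS without supervision". Home treatment follows: "From then on, TPNS will be executed daily in the family". Section 2.7 ties the clock to that moment: "The intervention period will be 4 consecutive weeks, immediately following the conclusion of the training period".

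**Outcome.** The Discussion puts applicability in the main aim: "This study's main objective was to assess the applicability and clinical outcomes of TPNS in children with FC". Section 2.9 ranks it lower: "As a secondary outcome, the applicability of TPNS will also be evaluated through the results of a specific questionnaire". Section 2.8 specifies that this questionnaire concerns the daily TPNS sessions at home.

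**Who is kept.** Table 1 in section 2.4 has a row for "Patients who do not complete the intervention or do not participate in some of the evaluation interviews". By its content this is an exclusion, whichever column the extracted table shows it in.

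**What comes before training ends.** Section 2.3 describes a first contact: "Patients will be invited to participate in an initial consultation to inform them about the research methods and apply eligibility criteria". Section 2.7 places the first interviews at "1 week before the start of the intervention, immediately after the 4 weeks of intervention". It does not say whether the baseline interview precedes training or falls within it.

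**The concern.** TPNS is delivered here by parents at home. A natural question about applicability is how many families who are offered the method and try to learn it end up able to use it. A family that trains and never feels able to work unsupervised, or leaves during training, is the plainest negative answer to that question.

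The stated rules leave this answer no way into the result. The instrument, the thing it rates and the start of the intervention are all fixed after the point at which such a family would be lost. The Table 1 row adds a second filter, on completion. What remains is the opinion of those for whom the method worked well enough to finish.

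A reader of the final report could take a high applicability rating as describing children with functional constipation in general. It would describe a group selected on early success with the technique. In a study of about 28 patients, a handful of families is enough to change the impression.

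**Working it through.** **1. The plan's own figure.** Section 2.3 gives a mean change of 18, a standard deviation of changes of 30, two-sided alpha 0.05 and power 0.85.

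- Standardised effect: 18/30 = 0.60.
- Normal approximation: ((1.960 + 1.036)/0.60)² = 24.9, so 25 patients.
- Exact paired t-test (noncentral t): 27 patients give power 0.851, and 28 give 0.864.

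The stated 28 is reproduced closely enough and is not in dispute. It serves below only as a plausible number of raters.

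**2. Following a family through the rules.**

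| Stage | Source | Family that becomes confident and completes | Family that stops in training |
|---|---|---|---|
| Initial consultation, eligibility | 2.3, 2.4 | present | present |
| Baseline interview | 2.7 | present | possible; order relative to training not fixed |
| Training | 2.5 | ends with confidence | does not reach that end point |
| Start of the 4-week period | 2.7 | yes | never |
| Daily home sessions | 2.5 | yes | none |
| Interviews after the intervention | 2.7 | yes | none scheduled, since their dates count from the intervention |
| Rating of home sessions | 2.8, 2.9 | yes | nothing to rate |
| Table 1 row on completion and interviews | 2.4 | kept | removed, on an ordinary reading |

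The right-hand column never reaches the applicability outcome. A family that begins at home and later stops has some home sessions to rate, but the last row removes it.

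**3. How much this could matter.** Let r be the share of 28 raters who find the method applicable, and f the number of further families who started training and did not reach unsupervised use. With those families counted as not applicable, the share among all who started training is

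r × 28/(28 + f).

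The documents give neither r nor f, so both are assumed.

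| f | Share lost in training | Result if r = 100% | Result if r = 90% |
|---|---|---|---|
| 3 | 3/31 = 9.7% | 28/31 = 90.3% | 0.9 × 28/31 = 81.3% |
| 7 | 7/35 = 20.0% | 28/35 = 80.0% | 0.9 × 28/35 = 72.0% |
| 12 | 12/40 = 30.0% | 28/40 = 70.0% | 0.9 × 28/40 = 63.0% |

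The fall equals r times the share lost in training. With no losses (f = 0) there is no overstatement from this source. Later non-completers removed by Table 1 would act in the same direction if they too were counted as not applicable.

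**The case against.** The best defence is that training carers before unsupervised home use is sound design, and that section 2.8 chooses to measure the applicability of home sessions, which only home users can judge. Uptake among everyone who starts training is a different quantity. Denominators and session logs are also details that a condensed article may leave to the full protocol. Training is legitimate, and nothing here argues against it. But the article does not merely omit a detail. It fixes the instrument, what is rated, the start of the intervention and an exclusion for non-completion, and together these determine whom the result describes.

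A reader might infer several stronger things that the documents do not support:

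- **That families who give up in training are lost before anyone counts them.** Consultation and eligibility come first, and baseline may fall before or during training. Section 2.11 promises reporting to CONSORT, and the flowchart in Figure 2 is not shown. They may well be counted in the flow. A flow count would still not put them into the applicability result.
- **That only families who mastered the technique are rated.** The text asks for confidence, and section 2.5 provides a supervised recheck every 15 days. Difficulties that arise after training can still be recorded.
- **That the training effort is left out of the assessment.** The questionnaire is in Supplemental Digital Content 10, which was not available, so its content cannot be judged.
- **That training drop-outs escape the Table 1 row because they never began the intervention.** A family that never starts also does not complete and misses interviews. On an ordinary reading the row covers it, and either way it is absent from the result.
- **That the percentages above estimate a bias.** The protocol defines no applicability proportion and gives no training-failure rate. That families will give up at all is an inference.

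**Conclusion.** The point holds in a limited form. Followed as written, the applicability result describes families who became confident after training of no stated limit and then completed the intervention. It cannot register a family that starts training and never reaches unsupervised use. If such families exist, the result will tend to overstate how applicable home TPNS is.

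The size is unknown. The falls from 100% to about 90%, 80% or 70% rest on three assumptions: 28 completing raters, all favourable, and 3, 7 or 12 training losses. They show scale only. The direction rests on the reasonable view that a family unable to reach home use is a negative finding on applicability.

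This is a worthwhile improvement to an outcome named in the main objective. It does not affect the sample size or the comparisons of bowel outcomes planned in section 2.10. The differing status of applicability in the Discussion and in section 2.9 is a separate inconsistency that the same edit can settle.

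**What to change.** 1. In section 2.9, report applicability with all consented families who start training as the denominator. Count those who leave during training, or do not reach unsupervised use, as not applicable.
2. State in section 2.4 or 2.9 that the Table 1 row on completion and interviews does not remove these families, or later non-completers, from this outcome.
3. Have the supervising physiotherapist log the number of training sessions for each family and the reason for any stop, and report both beside the applicability result.
4. Keep the questionnaire as the description of practical difficulties among those who treat at home.
5. Give applicability the same status in the stated objective and in section 2.9.

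The cost is a few sentences and a small log kept by someone who already supervises the procedures. No visit is added, and the training and treatment rules stay as they are. The drawback is a less favourable applicability figure. The log should start with the first family trained, since reasons for stopping may be hard to recover later.

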### Adherence to treatment and related adverse events

2.6

The biweekly-supervised TPNS sessions will be registered by the studies, also investigating the possibility of adverse events. During the research process, patients/parents/guardians can contact the research team by phone to communicate possible adverse events and clarify any questions.

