### Assessment interviews

2.8

In all assessment moments, patients and/or their guardians will participate in semi-structured interviews to determine the results of interventions regarding bowel movements and quality of life. The same member of the research team will be responsible for the interviews that will last approximately 40 minutes. The following surveys will be applied: a questionnaire addressing the current clinical status developed by our research group and previously used in another study that evaluated the impact of transcutaneous posterior tibial nerve stimulation in children and adolescents with FC^[31]^ (see questionnaire, Supplemental Digital Content 4); the modified Bristol Stool Form Scale for children (mBSFS-C)^[32–34]^ to analyze the stool consistency (see mBSFS-C, Supplemental Digital Content 5); the Bowel Function Score (BF-S)^[35]^ to evaluate the functional status of bowel habits (seeBF-S, Supplemental Digital Content 6); the Fecal Continence Index (FCI) questionnaire,^[36,37]^ based on the clinical evaluation of fecal continence (see FCI, Supplemental Digital Content 7); the Assessment of Quality of Life in Children and Adolescents with Fecal Incontinence (AQLCAFI)^[36,37]^ (see AQLCAFI, Supplemental Digital Content 8) and the Pediatric Quality of Life Inventory version 4.0 (PEDsQL 4.0)^[38,39]^ to assess the quality of life (see PEDsQL 4.0, Supplemental Digital Content 9). Lastly, a questionnaire addressing the evaluation of the applicability of the TPNS daily home sessions^[31]^ also developed and already used by our research group (see applicability questionnaire, Supplemental Digital Content 10).

In addition, patients will be monitored using a standardized week diary (stool frequency, stool consistency according to the mBSFS-c, frequency of fecal incontinence episodes, painful defecation, abdominal pain, excretion of blood in the stool, laxative use and their doses, and adverse effects such as pain, nausea, vomiting, diarrhea, and flatulence). The fulfilment of this diary will start seven days before each assessment moment. The doses of laxative medications will be registered, addressing any alterations as possible outcomes in the study's conclusion.

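### The adherence section describes a record only of the fortnightly supervised sessions, so the delivered home dose and partial adherence cannot be quantified, yet non-completers are excluded after enrolment

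*Protocol article*

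**What the plan says.** Section 2.5 of the protocol article sets the treatment: "A 500-μs, 10-Hz current will be applied 30 minutes daily for 4 or 8 consecutive weeks in the patient's residence". Parents are trained first, and then "From then on, TPNS will be executed daily in the family". During treatment, "patients will need to attend a supervised session of TPNS every 15 days for a revaluation of the technique and clarification of any doubts". The same section also says that a physiotherapist "will supervise all the procedures".

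Section 2.6, the section on adherence, states: "The biweekly-supervised TPNS sessions will be registered by the studies, also investigating the possibility of adverse events". It mentions no record of the home sessions.

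Section 2.8 describes a diary of stools, incontinence, pain, blood in the stool, laxatives and adverse effects. Stimulation sessions are not among the listed items. On timing it says: "The fulfilment of this diary will start seven days before each assessment moment".

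Table 1 in section 2.4 gives this among the grounds for exclusion: "Patients who do not complete the intervention or do not participate in some of the evaluation interviews".

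On applicability, the Discussion states that the study's "main objective was to assess the applicability and clinical outcomes of TPNS in children with FC". Section 2.9 makes applicability a secondary outcome, taken from a dedicated questionnaire on practical difficulties and adverse events.

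**The concern.** Nearly all of the treatment is given out of the team's sight, and the article describes no contemporaneous record of whether it was given. Two things depend on such a record.

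- **Interpretation.** If bowel function changes little, the described data cannot show whether the children received most of the planned sessions or far fewer.
- **Who is analysed.** The completion rule in Table 1 can only operate after enrolment. Without a threshold or a session record, a child with patchy home use could be kept or removed on judgement. In a single-arm before-and-after study, removing such children can shift the result.

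Sessions that were not recorded at the time cannot be recovered by any later analysis plan.

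**Working it through.** The plan states no figure for the share of sessions recorded, so there is none to reproduce. The share follows from its schedule.

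**Inputs**
- One session per day for 4 or 8 weeks (section 2.5): 4 × 7 = 28 or 8 × 7 = 56 planned sessions. Training comes before this period (section 2.7) and is not counted.
- One supervised session every 15 days (section 2.5): 28/15 = 1.9, so 1 to 2 sessions; 56/15 = 3.7, so 3 to 4 sessions.
- Assumption: a supervised session takes the place of that day's home session.

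**Share of planned sessions in the record** = supervised sessions / planned sessions

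| Period | Supervised | Recorded | Not recorded |
|---|---|---|---|
| 4 weeks | 1 of 28 | 3.6% | 96.4% |
| 4 weeks | 2 of 28 | 7.1% | 92.9% |
| 8 weeks | 3 of 56 | 5.4% | 94.6% |
| 8 weeks | 4 of 56 | 7.1% | 92.9% |

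A steady rate of 1 in 15 gives 6.7% recorded and 93.3% not recorded. If supervised sessions were instead additional to the daily home session, none of the home sessions would be in the record.

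**Could the diary fill the gap?** Not as described, because its listed items contain no stimulation entry. Its window is also too short. Treatment-period assessments come after week 4 and, for families who extend, after week 8 as well (section 2.7). The diary therefore covers 7 of 28 treatment days, or 14 of 56, which is 25% in both cases. Adding a session item to the diary as timed would still miss three quarters of the treatment.

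**What can be seen about completion?** Withdrawal, a family reporting that it has stopped, a missed supervised visit and a missed interview would all come to light. A child who attends every visit but receives only some of the home sessions would look the same, in the records described, as a child who receives all of them. Table 1 gives no number of sessions that would separate the two.

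**The case against.** **Applicability.** A reader might infer that applicability cannot be established at all. The documents do not support that. Sections 2.8 and 2.9 define it through a questionnaire on the home sessions, and that questionnaire is administered. The share of sessions delivered would be a useful addition, but it is not the plan's own definition.

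**Absence of any record.** Section 2.6 does not say that nothing else is recorded. The applicability questionnaire, the clinical questionnaire and the SPIRIT supplement are cited but not shown, and they may contain recall items on sessions. What can be said is that the article describes no session-level home record. Against that, the article does set out what is registered for adherence and what the diary contains, so the point concerns stated choices and not mere brevity.

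**Recall.** It is tempting to say that families would have to recall up to 8 weeks. They would not: interviews fall about 4 weeks apart during treatment and supervised visits 15 days apart, so recall would be about 2 to 4 weeks. A daily log is still better than that.

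**Power.** A reader might translate under-delivery into lost power. That needs an effect proportional to sessions delivered, which the documents do not state. It would also measure the cost of poor adherence, which a log does not repair; sample size and power are the same with or without one.

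**Self-report.** A family log handed to the team that trained the family shares the questionnaire's reporting bias. This stands: the log improves recall, not candour.

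**Supervision.** Taken literally, the statement that a physiotherapist supervises all procedures would leave no unsupervised sessions. It conflicts with daily home use by trained parents in the same section, and the two statements must be reconciled.

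**Conclusion.** The point holds in a limited form. The records described cover about 4% to 7% of planned sessions, so the delivered home dose cannot be quantified and partial home adherence cannot be seen. The completion exclusion in Table 1 has neither a threshold nor a session record behind it and acts after enrolment. Gross non-completion remains visible, and applicability as the plan defines it is measured.

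The percentages rest on the stated schedule and on a supervised session replacing that day's home session. The finding on records assumes that the supplements not shown contain no daily session record. This is a low-cost improvement to what is recorded and who is analysed. It is no ground for changing the sample size.

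**What to change.** 1. Add a one-line daily home log (session done yes/no, minutes) for the whole 4 or 8 weeks, and collect it at the existing fortnightly visits.
2. Report the percentage of planned sessions delivered with a 95% CI, alongside the applicability questionnaire. Calculate the percentage for each child first, because sessions within a child are not independent.
3. Describe completion from the log, and keep enrolled low-adherence children in the outcome analysis instead of excluding them. Amend the Table 1 entry to match. Children who miss interviews are a separate missing-data matter that a log does not solve.
4. Reconcile the statements in section 2.5 on who supervises the sessions.

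The cost is a short amendment needing ethics committee approval (section 2.11) and slightly more diary burden for families. No extra visits or patients are needed. The log will still be family self-report, and the report should say so.
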